### 2.9. Sample size

The sample size calculation for this study was established using the G Power software, version 3.1.9.2 (available at: http://www.gpower.hhu.de/), which considered Cohen effect size of 0.80, power test of 0.80 and significance level of 5% (*P* < .05). Thus, a total sample of 39 patients was obtained, with 13 participants assigned to the Control Group (CG) and 26 to each Intervention Group (GI1 and GI2).

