Results favorable to the use of different nasally placed small-bowel feeding tube insertion methods have been described by anesthesiologists.^[11–13]^ Among these, the lateralized head^[5,12]^ and the use of the laryngoscope^[11]^ stand out. Such studies have demonstrated nasally placed small-bowel feeding tube insertion methods that are faster, more effective and that cause less complications to patients. However, it is clear that such techniques are little used by nurses in clinical practice. It is important and necessary for nurses to be able to offer safer care with less risk of complications, based on the best available evidence, through the possibility of revealing the most adequate, effective, fast and safe technique to improve the execution of this procedure.

In a study conducted in Taiwan, 130 insertion attempts were performed. The success rate was 82.7% (86 of 104 patients) on the first attempt and 100% in 5 attempts. In 23 patients the tube deviated to the oral cavity and 3 to the trachea.^[15]^ Verification of vital signs are important to detect clinical deterioration of the patient.^[16]^

We seek to test the following hypothesis: null hypothesis: There are no significant differences between the methods of insertion of the nasally placed small-bowel feeding tube in patients in coma (physiological or induced) and intubated in relation to the rate of success in the first attempt, insertion time and the presence of complications; alternative hypothesis: There are significant differences between the methods of nasally placed small-bowel feeding tube insertion in comatose patients (physiological or induced) and intubated in relation to the rate of success in the first attempt, insertion time and the presence of complications.

Therefore, the study aims to determine the effectiveness of different nasally placed small-bowel feeding tube insertion techniques in coma and intubated patients, in comparison with conventional method.

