### 2.8. Endpoint

#### 1.2.8. Primary outcome.

The success rate on the first attempt will be considered as the dependent variable. Insertion success will be defined as the successful passage of the tube on the first attempt and confirmed by radiography of the correct anatomical positioning of the tube distal tip, which will be performed immediately after the procedure. If the nasally placed small-bowel feeding tube is not successfully inserted, it will be considered a failure and recorded as an unsuccessful attempt. Subsequently, new attempts will be performed.

The number of attempts required for successful insertion will be recorded for each patient. It should be noted that if more than 3 attempts are required, the procedure will be declared unsuccessful and data will be used to count failures. In these cases, the researchers may use another method of free choice for nasally placed small-bowel feeding tube insertion.

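### Section 2.9 derives 39 patients from an effect size of 0.80, but no standard test for this design gives 39 from that input, and the protocol does not say which comparison has the 80% power

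*Protocol article*

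**What the plan says.** Section 2.9 says the sample size was "established using the G Power software, version 3.1.9.2", "which considered Cohen effect size of 0.80, power test of 0.80 and significance level of 5"%, and that from these inputs "a total sample of 39 patients was obtained". It does not name the effect-size index (d, h, w or f), the test, the sidedness or any assumed success rate. It then puts 13 patients in the control group and 26 in each of the two intervention groups. Section 2.10 divides 39 patients into three groups.

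The primary outcome is binary: "The success rate on the first attempt will be considered as the dependent variable" (section 2.8). The Introduction states the aim as finding the effectiveness of the techniques "in comparison with conventional method". Its alternative hypothesis is global and has no direction: "There are significant differences between the methods of nasally placed small-bowel feeding tube insertion in comatose patients". Section 2.14 names chi-square, Fisher or ANOVA as the tests.

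**The concern.** The section prints both the inputs and the output of a calculation, so the two can be checked against each other, and they do not match. This is not detail that an article leaves to a fuller document. At least one printed figure is wrong, or the calculation was for something other than a three-group comparison.

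The stated power guides how a non-significant result is read. Readers will see 80% power beside an aim framed against the conventional method and may assume that it applies to each technique against control. If the true power of those comparisons is much lower, a non-significant result could be taken as evidence of no difference when the trial had little chance of showing one.

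**Working it through.** **Inputs.** Effect size 0.80, power 0.80, alpha 0.05, total 39 (section 2.9); three groups (section 2.10); binary primary outcome (section 2.8). Tests are taken as two-sided because the hypothesis has no direction.

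**Step 1: can 39 be reproduced from 0.80?**

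Chi-square: N = λ / w², where λ is the noncentrality that gives 80% power. λ = 7.849 for 1 df and 9.635 for 2 df.

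| Reading of 0.80 | Calculation | Result |
|---|---|---|
| w, chi-square 1 df | 7.849 / 0.64 = 12.3 | 13 in total |
| w, chi-square 2 df (three groups × success/failure) | 9.635 / 0.64 = 15.05 | 16 in total |
| f, three-group ANOVA, equal groups (noncentral F) | power 79% at N = 18, 86% at N = 21 | 21 in total |
| d, two-sided t-test (noncentral t) | power 79% at 25 per arm, 81% at 26 | 26 per arm: 52 for two arms, 78 for three |
| d, one-sided t-test | noncentral t | 21 per arm: 42 for two arms |

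None gives 39. The nearest miss is a one-sided, two-group normal approximation (38.6 unrounded, so 20 per arm, 40 in total). It has two groups rather than three, does not fit a hypothesis without direction, and is not G*Power's t-test, which gives 42.

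**Step 2: what does give 39?** A 2-df chi-square with w = 0.50: 9.635 / 0.25 = 38.5, rounded up to 39 (power 80.5%). A second conceivable route is the 1-df total of 13 at w = 0.80, taken as a per-arm size and tripled. The protocol confirms neither.

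**Step 3: group sizes.** 13 + 26 + 26 = 65, not 39. Equal thirds, 13 + 13 + 13 = 39, is the only split that fits, with 26 being the two intervention groups together. That is an inference.

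**Step 4: power of one technique against control.**

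- 0.80 as d, 13 v 13: noncentrality 0.80 × √(13 × 13 / 26) = 2.04, critical t (24 df) = 2.064, power 50%.
- 0.80 as d, 13 v 26: noncentrality 0.80 × √(13 × 26 / 39) = 2.36, critical t (37 df) = 2.026, power 63%.
- w = 0.50 with 26 patients, 1 df: λ = 26 × 0.25 = 6.5, power 72%.
- w = 0.80 with 26 patients, 1 df: λ = 26 × 0.64 = 16.6, power 98%. In two equal arms this means about 10% v 90% success: 0.80 / (2 × √(0.5 × 0.5)) = 0.80.

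**Step 5: power on first-attempt success at 13 v 13.** The rates are assumed, because section 2.9 gives none. Power is by full enumeration of both binomials, two-sided alpha 0.05.

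| Control v technique | Fisher | Pearson chi-square |
|---|---|---|
| 60% v 90% | 28% | 43% |
| 50% v 90% | 49% | 66% |
| 40% v 90% | 71% | 84% |

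Both tests are shown because section 2.14 allows either.

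**The case against.** The strongest reply is that the protocol never claims 80% power for a comparison with control. That stands. Section 2.9 attaches its power to no comparison, and the hypotheses concern differences among the methods as a whole. A reader might infer from the stated aim that 80% was promised for each technique against control, but the text does not say so. Low pairwise power is therefore a matter of design and disclosure. The arithmetic error is the mismatch between 0.80 and 39.

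Three other stronger readings also go too far:

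- **That no route to 39 leaves adequate pairwise power.** If 0.80 is w and 13 was tripled, a 13 v 13 comparison has 98% power for that effect. The difficulty is then the effect itself: nothing in the document supports about 10% v 90% success.
- **That non-significance is likely even for a large benefit.** This depends on the assumed rates and the test. At 40% v 90% power is 71% to 84%; at 50% v 90% it is 49% to 66%. Only 60% v 90% stays below one half with both tests. The 82.7% first-attempt success in the Introduction comes from an earlier study and is not tied to any arm here, so it cannot settle the control rate.
- **That w = 0.50 was the real input.** It fits exactly, and confusing the conventional large value of w (0.50) with that of d (0.80) is plausible, but this remains a guess until the calculation record is seen.

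None of this rescues the printed calculation. Whether 0.80 is w, f or d, the result is not 39.

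**Conclusion.** Section 2.9 is wrong as written: an effect size of 0.80 with 80% power at 5% does not give 39 patients under any standard test that suits three groups. The figures that do follow are 13, 16 or 21 in total, or 26 per arm. This rests only on the printed inputs and on taking the test as two-sided, and the one-sided t-test does not give 39 either.

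The power against control is undetermined because the index is not named: about 50% if 0.80 is d (63% at 13 v 26), about 72% if the input was w = 0.50, and 98% if 0.80 is w. These figures assume 13 per arm except where stated. The group sizes separately contradict the total, 65 against 39.

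**What to change.** Keep 39 patients and correct section 2.9:

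1. Retrieve the G*Power record and state the test, the effect-size index and the first-attempt success rates actually used. Do not write in w = 0.50 or a set of rates merely because they fit.
2. Correct whichever of 0.80, 39 or the power is wrong. If the record shows the 2-df chi-square, state w = 0.50 and that the 80% power is for the global three-group test only.
3. Make the group sizes agree with the total of 39.
4. State the actual power of each comparison with the conventional method under the stated rates and the chosen test, and say that a non-significant comparison will not be read as showing no difference.

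The cost is one reworded paragraph and a stated power that looks less favourable. Section 2.1 says data collection is ongoing, and the change affects neither recruitment nor procedures.

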### 2.6. Allocation

In this study, only data analysts will be blinded to the treatment group to which participants were randomized. However, resources will be used to minimize, as much as possible, biases in research results.

For this, there will be a collaborating researcher (P1), who will be responsible for the allocation and randomization of patients prior to data collection using computer-generated random numbers, to be carried out through the “Research Randomizer” website (https://www.randomizer.org), in addition to the application of the collection instrument, verification of the insertion time and annotation of the vital signs and application of the collection instrument, as well as the reading of the insertion X-ray, to be performed immediately after the insertion of the nasally placed small-bowel feeding tube. Three nurses (E1, E2, E3) will be in charge of applying any of the programmed techniques. It is noteworthy that nurses responsible for applying the techniques are from the service where the data collection will be carried out and work on the day and night shifts and will be unaware of topics to be evaluated. Although the nurses are aware of the method that will be used for the insertion of the tube, they will not be aware of the objectives of the study. This way, only the investigation team will know which technique was used in each patient, and patients will not know due to their clinical condition.

To minimize biases, it is noteworthy that, prior to the data collection stage, nurses were trained in relation to the techniques applied to familiarize with the procedure, as this fact can influence the success rate and the time required for insertion. To this end, a previously elaborated script will be strictly followed for each of the techniques, with nurses being trained in theory and laboratory practice. Materials and monitoring equipment used will also be standardized. The PHILIPS CM10 Efficia multiparameter will be used to monitor all patients and the nasally placed small-bowel feeding tube (EMBRAMED).

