### 2.10. Randomization and masking

Thirty-nine patients will be randomly divided into 3 groups. Patients allocated in the control group (CG) will have the tube inserted in the conventional way, that is, the head is kept in the neutral position, while the tube is gently inserted through one of the nostrils, without any maneuver or instrument.

Patients selected for the first intervention group (GI1) will have their heads turned to the right lateral position. This way, the tube will be inserted through the selected nostril without any neck maneuver or instrument.

For patients selected for the second intervention group (GI2), a conventional adult laryngoscope will be orally inserted. The tracheal tube and tongue will be raised to provide the best view of the larynx area. Thus, after viewing the piriform sinus or the esophagus, the tube will be inserted into the patient nostril and advanced to the esophagus under direct visualization. The patient head will be held in the neutral position and the blade will be gently lifted to avoid excessive neck extension.

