### 2.14. Data extraction and statistical analysis

Data will be analyzed using the Statistical Package for Social Science software, version 18.0 (SPSS Version 20.0), where descriptive and inferential analyses will be carried out, and results will be presented through tables, charts and figures. To evaluate variables, the Chi-square test (χ²) or Fisher test or ANOVA will be used. Other statistical tests that may be necessary will also be used. Significance level of 5% (*P* = .05) will be adopted.

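### The stated arm sizes (13 + 26 + 26 = 65) contradict the stated total of 39, and no visible text gives an allocation ratio

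*Protocol article*

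**What the plan says.** Section 2.9 (Sample size) of the protocol article reports a G*Power calculation with "Cohen effect size of 0.80", "power test of 0.80" and "significance level of 5% (*P* < .05". It concludes: "Thus, a total sample of 39 patients was obtained", and continues "with 13 participants assigned to the Control Group (CG) and 26 to each Intervention Group (GI1 and GI2". It does not name the test, the effect-size metric or the sidedness.

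Section 2.10 (Randomization and masking) says "Thirty-nine patients will be randomly divided into 3 groups", and the Abstract says the same. Neither gives arm sizes. Section 2.6 (Allocation) describes "computer-generated random numbers, to be carried out through the “Research Randomizer” website" and gives no ratio. Section 2.1 says that data collection is already under way.

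**The concern.** The only sentence that gives arm sizes contradicts the total that it gives. A reader cannot tell from the text whether 39 or 65 patients are planned, or whether allocation is 1:1:1 or 1:2:2.

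Three things depend on the answer: when recruitment stops, what the random list should contain, and how much information there is on each comparison with the conventional method. Because recruitment has started, a list presumably exists. Until the sentence is corrected, nobody outside the team can say whether the final arm sizes followed the plan.

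**Working it through.** **Step 1: add the arms (section 2.9).**

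- Literal reading: CG 13 + GI1 26 + GI2 26 = 65, ratio 1:2:2.
- Gap to the stated total: 65 − 39 = 26, and 26/39 = 67%.
- If 26 covers GI1 and GI2 together: 13 + 13 + 13 = 39, ratio 1:1:1.

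**Step 2: look for text that settles it.** The total of 39 stands in the Abstract, section 2.9 and section 2.10. Arm sizes stand only in section 2.9. None of these sections, nor section 2.6, states a ratio or says that the groups are equal. The flowchart (Figure 1) is not available in the text reviewed.

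**Step 3: try to recover 39 from the stated inputs** (effect size 0.80, power 0.80, alpha 0.05). Since test and metric are not given, several standard versions were tried:

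| Calculation | Size needed |
|---|---|
| Two-sided t-test, d = 0.80, 1:1 | 26 per arm (52 for two arms, 78 for three) |
| Two-sided t-test, d = 0.80, 1:2 | 20 + 40 = 60 |
| One-sided t-test, d = 0.80, 1:1 | 21 per arm (42 for two arms, 63 for three) |
| One-sided t-test, d = 0.80, 1:2 | 15 + 30 = 45 |
| One-way ANOVA, three equal groups, f = 0.80 | 21 in total |
| Chi-square, w = 0.80, 1 df | 13 in total |
| Chi-square, w = 0.80, 2 df | 16 in total |

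None gives 39 for three arms. A three-group ANOVA would reach 80% power at 39 only with f of about 0.52. The figures 13 and 26 each appear in the table, 13 as a total and 26 as a per-arm size, so the inputs do not show which of the two conflicting statements is the slip.

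**Step 4: confirm the 26.** For a two-sided t-test with arms n1 and n2, df = n1 + n2 − 2 and the noncentrality is δ = d × √(n1·n2/(n1 + n2)). Power is the probability that a noncentral t with these parameters falls beyond ±t(0.975, df).

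- 25 v 25: δ = 0.80 × √12.5 = 2.828, df 48, critical value 2.011, power 79.1%.
- 26 v 26: δ = 0.80 × √13 = 2.884, df 50, critical value 2.009, power 80.7%.

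So 26 per arm is exactly the smallest size that reaches 80%.

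**Step 5: what the two readings mean for a comparison with control**, with the same formula and 0.80 read as d (an assumption):

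- 13 v 13: δ = 0.80 × √6.5 = 2.040, df 24, critical value 2.064, power 49.9%.
- 13 v 26: δ = 0.80 × √(338/39) = 2.355, df 37, critical value 2.026, power 63.1%.

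**The case against.** The strongest reply is that this is a slip of the pen. The total of 39 appears three times and 65 never does. No section mentions 1:2:2, and 13 + 26 = 39 exactly if 26 is the two intervention groups combined. The missing flowchart may also show the arm sizes. Most of this stands: 13 per arm is the likeliest intention, and the remark about the ratio applies only to the visible text. It does not remove the contradiction, and Step 4 shows why the slip should be checked rather than presumed.

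A reader might go further in three ways that the document does not support.

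- **A shrunken control arm.** One might infer a 1:2:2 list stopped at 39, leaving about 8 controls. Section 2.9 gives 13 controls on either reading, so that split mixes two statements into a design nobody described.
- **Firm power figures for the success rate.** With assumed first-attempt success of 44% v 90% v 90%, a global chi-square test has power of about 80% at 13/13/13 and 93% at 13/26/26. These rates are not in the protocol, and the result moves a great deal with them: 70% and 86% at 50/90/90, and 19% and 25% at 82.7/95/95. The 82.7% is the first-attempt success in the cited Taiwanese study; the 95% is assumed. None of these figures shows that 39 is adequate.
- **A faulty random list.** Nothing shows that the list is wrong. It may well hold 13 per arm, in which case only the published sentence needs correcting.

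**Conclusion.** The contradiction is real and needs no assumption: the arm sizes exceed the stated total by 26 patients, 67% of 39, in the only visible text that defines them. This is neither detail left to a fuller document nor an effect of condensing the article, because the figures are stated and they conflict.

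That the intended design is 13 per arm, 1:1:1, is probable but unconfirmed. The pairwise powers of about 50% and 63% rest on reading 0.80 as d and on a two-sided 5% t-test without multiplicity adjustment. They show that the choice of reading matters, but they are not the trial's power for its primary outcome, which is a success rate. How serious the matter proves depends on the check: if the list holds 13 per arm it is a reporting correction, and if not, the trial's size and ratio differ from what most readers will assume.

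**What to change.** 1. Retrieve the saved G*Power output and the randomisation list in use, and establish the total, arm sizes and ratio that were intended and that are being applied.
2. Correct the sentence in section 2.9 so that the three agree, and state the ratio in section 2.10. If 39 is confirmed, write: *a total of 39 patients, 13 in each of CG, GI1 and GI2 (26 in the two intervention groups combined), allocated 1:1:1*. If it is not, state the confirmed total in section 2.9, section 2.10 and the Abstract.
3. If the list departs from the corrected statement, report the departure.

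No new list or blocking scheme is needed to resolve this; replacing the list while data collection is under way would itself be a change to the trial. If 39 is confirmed, the cost is one sentence and a check of the list.

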### 2.10. Randomization and masking

Thirty-nine patients will be randomly divided into 3 groups. Patients allocated in the control group (CG) will have the tube inserted in the conventional way, that is, the head is kept in the neutral position, while the tube is gently inserted through one of the nostrils, without any maneuver or instrument.

Patients selected for the first intervention group (GI1) will have their heads turned to the right lateral position. This way, the tube will be inserted through the selected nostril without any neck maneuver or instrument.

For patients selected for the second intervention group (GI2), a conventional adult laryngoscope will be orally inserted. The tracheal tube and tongue will be raised to provide the best view of the larynx area. Thus, after viewing the piriform sinus or the esophagus, the tube will be inserted into the patient nostril and advanced to the esophagus under direct visualization. The patient head will be held in the neutral position and the blade will be gently lifted to avoid excessive neck extension.

### 2.11. Data collection

A data collection printed form containing variables about patients will be used, namely: Identification (bed; name initials; age; sex; date of birth); Clinical data (cause of admission; estimated weight, height and body mass index); Level of consciousness or Ramsay scale data, including type of drug used and sedation duration; Endotracheal tube number and cuff pressure; Data regarding the technique used (technique; number of attempts; required time in seconds; complications, if any); Parameters to be evaluated (heart and respiratory rate, blood pressure and oxygen saturation) before, during and after nasally placed small-bowel feeding tube insertion using each of the techniques; Confirmation of the correct nasally placed small-bowel feeding tube positioning by chest and abdomen radiography in bed.

Table 1 shows the detailed study stages, with the Standard Protocol Items for Randomized Trials schedule of enrollment, interventions, and assessments.

**Table 1 T1:** Description of the study stages: P1: Day 1—request for nasally placed small-bowel feeding tube insertion in the patient and intervention. F1: evaluation after the procedure until X-ray is performed.

Study period					
			Post-allocation: Allocation, interventions, follow-up		
Timepoint	Enrollment	Baseline	Allocation	P1 intervention	Follow-up (F1)
Enrollment:					
Eligibility criteria	X				
Recruitment	X				
Initial assessment	X				
Informed consent	X				
Allocation			X		
Interventions:					
Insertion in a conventional manner (control group)				⟷	X
Insertion with the head turned to the right side (intervention group)				⟷	X
Insertion with laryngoscope (intervention group)				⟷	X
Assessments:					
Identification, clinical data, level of consciousness, SSVV, among others		X			

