## Abstract

**Methods::**

A prospective, randomized and controlled clinical trial will be carried out with coma and intubated patients admitted to the Intensive Care Unit (ICU). Thirty-nine patients will be randomly divided into 3 groups: group who will have the tube inserted in a conventional manner with the head in the neutral position, group with the head positioned laterally to the right, and, finally, with the head in the neutral position, with assistance of a laryngoscope. The primary endpoint will be: first, second and total attempt success rate; and time required for the first successful attempt and the sum of all attempts. Complications during insertion included tube bending, twisting, knotting, mucosal bleeding, and insertion into the trachea. Patient vital signs will be measured.

Strengths and Limitations of this Study•This is a single-center study, and participants will be recruited from a single hospital, which compromises the generalisability of the findings;•Blinding of nurses will not be possible;•The instrument used did not go through the face and content validation process.

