#### 2.2.8. Secondary outcome.

Secondary endpoints will be time required and associated complications. The time required will be recorded from the nasally placed small-bowel feeding tube insertion from the nostril to the calculated length of the tube with the aid of a stopwatch. The insertion times for each attempt will be counted and, in case of failures, the time required for each attempt will be added together.

In addition, AEs associated with the insertion techniques (bleeding of the visible mucosa, nasal mucosa edema, in addition to tube bending, twisting, knotting and insertion into the trachea visible on X-ray) will be recorded. It is noteworthy that the occurrence of bleeding will be considered as visible bleeding in the tube extension and nasal or oral mucosa. The analysis of such AEs will be performed immediately at the end of the procedure until radiological confirmation of the tube positioning and previous removal of the guide wire. The radiograph will be performed on the patient bed and the patient will be kept in the same position, in the supine position. If the patient shows signs of respiratory distress during insertion, the procedure will be stopped.

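### Vital signs are recorded before, during and after insertion, but the pre-insertion value has no stated role in the analysis; ANCOVA would use it at almost no cost

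*Protocol article*

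**What the plan says.** Section 2.11 (Data collection) has the form record oxygen saturation, blood pressure, heart rate and respiratory rate "before, during and after nasally placed small-bowel feeding tube insertion using each of the techniques". Table 1 also places vital signs (SSVV) in the baseline column, so a pre-insertion value is planned for every patient.

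Section 2.14 (Data extraction and statistical analysis) gives the methods in one sentence: "To evaluate variables, the Chi-square test (χ²) or Fisher test or ANOVA will be used". It then adds: "Other statistical tests that may be necessary will also be used". No test is tied to a particular variable, the form of ANOVA is not given, and no covariate, change score or repeated-measures structure is mentioned.

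On the standing of vital signs, the abstract says only "Patient vital signs will be measured". The primary outcome is first-attempt success ("The success rate on the first attempt will be considered as the dependent variable"), and on the rest Section 2.8 says "Secondary endpoints will be time required and associated complications". The hypotheses in the Introduction cover success, time and complications. The Introduction mentions vital signs as a means of noticing that a patient is getting worse.

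**The concern.** ANOVA is the only one of the three named tests that suits a continuous measurement such as heart rate or oxygen saturation. Vital signs vary widely between intensive-care patients before anyone touches the tube, and much of that variation is likely to persist during the procedure. An analysis that does not condition on the patient's own starting value carries the between-patient variation into the comparison of techniques. With about 13 patients per arm, it also lets chance differences at the start pass into the result.

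The stakes are modest. The comparison would inform the tolerability of each technique and would not decide the trial's main question. But the pre-insertion values are already being collected, and leaving their use open also leaves open a choice among post-only, change-score and adjusted analyses for four signs at two later times. Section 2.1 says data collection is ongoing, so the choice can still be written down before analysis.

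**Working it through.** The article gives no precision or power figure for vital signs, so there is none to reproduce. The sample-size statement in Section 2.9 is not tied to them.

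**Inputs**
- Three arms and 39 patients in total (Sections 2.9 and 2.10). I take 39/3 = 13 per arm. This is an assumption: Section 2.9 also states 13 control patients and 26 in each intervention group, and 13 + 26 + 26 = 65 does not match 39.
- Correlation r between the pre-insertion value and the value during or after insertion: not in the article, so assumed, with a range of 0.3 to 0.7.
- Equal SD at the two times and the same r in every arm: assumed.
- A true difference of 0.8 SD between two arms, two-sided 5%: chosen for illustration only. Section 2.9 uses an effect size of 0.80 but does not link it to vital signs.

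**Variance of a between-arm difference, relative to ANOVA on the post-insertion value alone (= 1)**
- ANOVA of the change from the pre-insertion value: 2(1 − r)
- ANCOVA with the pre-insertion value as covariate: 1 − r²
- ANCOVA relative to change score: (1 − r²) / [2(1 − r)] = (1 + r)/2, which is below 1 for every r below 1

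| r (assumed) | Change score, 2(1 − r) | ANCOVA, 1 − r² | ANCOVA / change score, (1 + r)/2 | Equivalent n per arm, 13/(1 − r²) |
|---|---|---|---|---|
| 0.3 | 1.40 | 0.91 | 0.65 | 14.3 |
| 0.5 | 1.00 | 0.75 | 0.75 | 17.3 |
| 0.6 | 0.80 | 0.64 | 0.80 | 20.3 |
| 0.7 | 0.60 | 0.51 | 0.85 | 25.5 |

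The ANCOVA standard error is √(1 − r²) of the post-only one: 0.95, 0.87, 0.80 and 0.71 at r = 0.3, 0.5, 0.6 and 0.7. At r = 0.5 the change score gains nothing over the post-only analysis, and below 0.5 it is worse.

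**Power, two arms of 13, difference 0.8 SD** (noncentral t for post-only; simulation for ANCOVA, good to about 0.01)
- Post-only: 0.50 at any r.
- Change score: equals the post-only power at r = 0.5, where the variances are the same; about 0.58 at r = 0.6 and 0.71 at r = 0.7.
- ANCOVA: about 0.52 at r = 0.3, 0.59 at 0.5, 0.66 at 0.6 and 0.76 at 0.7.

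**Power, overall three-arm F test, N = 39, assumed f = 0.4** (noncentral F; ANCOVA has 35 residual degrees of freedom instead of 36)
- Post-only: 56%.
- Change score: 43%, 56% and 80% at r = 0.3, 0.5 and 0.7.
- ANCOVA: 61%, 70% and 86%.
- At r = 0 ANCOVA has 56.3% against 56.4% for post-only, so the lost degree of freedom costs practically nothing.

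**Chance imbalance before insertion.** The standard error of a difference between two arm means is √(2/13) = 0.39 SD. For one comparison, a gap above 0.5 SD corresponds to |z| > 0.5/0.39 = 1.27, with probability about 0.20. The probability that at least one of the two techniques differs from the shared control by more than 0.5 SD is about 0.34.

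**The case against.** The strongest reply is that the article does not state the analysis being criticised. A reader might infer from Section 2.14 that the pre-insertion value is thrown away, but the text does not support that. It assigns no test to vital signs, does not say one-way or post-insertion only, and leaves further tests open. ANOVA may mean a change-score or technique-by-time analysis, both of which use the pre-insertion value, and at r = 0.7 the change score recovers most of the gain (80% power against 86% for ANCOVA and 56% for post-only). The exact model may also stand in a full protocol or analysis plan that is not shown.

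A reader might likewise infer that vital signs are the trial's main tolerability result. They are not named as a primary or secondary endpoint and do not appear in the hypotheses, and no between-arm comparison of them is announced.

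Both points stand, and they limit the concern to a recommendation. They do not remove it. With one later time point, the technique-by-time contrast is the change-score comparison, so the variance comparison above covers it. Under either reading of ANOVA, ANCOVA is the more precise analysis for every r strictly between 0 and 1.

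**Conclusion.** The point holds as a low-severity, no-regret improvement. The article plans a pre-insertion measurement, names ANOVA as its only continuous-data method, and gives the earlier value no stated role. Nothing in it is contradictory or wrong on this point.

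The size depends on a correlation the article does not supply. At r = 0.5 to 0.7, ANCOVA removes 25% to 49% of the variance of a post-only analysis, and 25% to 15% of that of a change-score analysis. At r = 0.3 the gain over post-only is about 9% of the variance and hardly visible in power (0.52 against 0.50), although the gain over a change score is then larger (35%). The figures assume 13 per arm, equal SDs over time and a common correlation across arms; the power figures also rest on illustrative effect sizes. The first-attempt success, time and complications analyses are not affected.

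**What to change.** Add one sentence to Section 2.14: any between-arm comparison of a vital sign during or after insertion is made by ANCOVA, with that sign's own pre-insertion value as covariate, and each technique is reported against control as an adjusted mean difference with 95% CI. Vital signs can keep their present standing as a supporting safety measure; they need not become an endpoint.

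The cost is wording and one residual degree of freedom per model. No further measurements or patients are needed. Since data collection is under way, the sentence should be fixed and dated before the comparisons are run.
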